### Study aims and hypotheses

The hypothesis of this project is that self-administered RA will result in improvements in measures of PCRF, quality of life, and sleep quality, compared to SA and standard of care. To assess this hypothesis, our primary aim is to examine the effect of 6-weeks of RA compared to a regimen of SA or standard of care on fatigue as assessed by:

A. weekly self-report using the Brief Fatigue Inventory (BFI), our primary outcome.

B. objective daytime physical activity on a wrist worn accelerometer using average activity counts/minute.

C. fatigue severity assessed 4 times daily using a visual analog scale recorded on wrist-worn accelerometer.

D. quality of life as assessed by Long Term Quality of Life Instrument (LTQL).

Our secondary aims include investigating the effect of 6-weeks of RA compared to a regimen of SA or standard of care on sleep quality of BC survivors as assessed by:

A. monthly self-report using the Pittsburgh Sleep Quality Index (PSQI), our primary outcome.

B. daily sleep/wake diaries and nighttime actigraphy.

C. examining the relationships between improvements in sleep quality and improvements in quality of life for SA and RA, as assessed by LTQL.

Our other secondary aim is to assess activity parameters required for implementation of an acupressure treatment in a clinical setting including the time to onset of a clinically meaningful effect as well as the duration of effect following cessation of the intervention. These factors are currently unknown for acupressure.

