### Objective study measure

#### Actiwatch-S is used to collect daytime and nighttime physical activity and symptoms

This wrist-worn accelerometer monitors the occurrence and degree of motion and measures the number of movements that exceed 0.01 g gravitation force. Activity data are downloaded to computer and sleep/wake activity is estimated using Actiware^®^ – Sleep software. It is important to emphasize that actigraphy does not measure sleep per se, but a behavior that is highly correlated with sleep—level of activity. Sleep episodes, both intended and unintended, can be reliably identified when low activity occurs in the presence of other indicators of sleep, such as self-reported sleep
[26-29]. Participants are instructed to wear the Actiwatch-S at all times. If the Actiwatch-S is removed, removal and replacement times are recorded in a daily log book. The software uses a validated algorithm to compute standard parameters of sleep/wake and activity cycles for each day of recording, which are checked by our study staff using the log books. The primary outcomes for nighttime actigraphy are total sleep time (total minutes scored as sleep by the Actiware^®^ algorithm) and sleep efficiency (total sleep time/time in bed*100,%).

Actigraphy has also more recently been used by members of our research team to examine daytime physical activity by measuring activity patterns
[28-32], the effects of a physical activity intervention
[30], and to assess fatigue. The assessment of fatigue using this method improves upon existing recall-based methods of symptom reporting in which people tend to underreport or report only peak or recent symptoms
[33] Figure
2.

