## Statistical issues

### Statistics and power analysis

Primary Aim: The primary aim of this study is to investigate the differential effects of different modes of acupressure on fatigue in breast cancer survivors. For this, we are focusing on three fatigue outcomes, namely, BFI, which will be administered weekly, a measure of average daily physical activity and a self-reported fatigue score, both based on Actiwatch-S data. A BFI is collected weekly and provides a measure of average degree of fatigue, a score that ranges between 0 and 10, with higher numbers indicating more fatigue. We will be analyzing the BFI outcome over phases. The first phase BFI is obtained by averaging week-1 to week-3 measures (mid-treatment). The second phase comprising of week-4 to week-6 measures indicates the status in the second half of the treatment phase (end-treatment). The final phase comprises of week-7 to week-10, the washout phase (washout). In order to investigate the change in BFI between the three study arms, we are using a mixed-effects regression analysis with average BFI in the three phases as the outcome, phase as the within-subjects factor, and group (RA, SA, standard of care) as the primary between-subjects factor. The baseline BFI level will be used as a covariate. We shall further adjust the model for key demographic variables such as age and ethnicity, as well as the baseline HADS score. A *subject* random-effect will be used to account for the clustering effect within the three measurements on the same subject. Of primary interest is the group*phase interaction, the significance of which will indicate differences in extent of decrease between the arms. Post-hoc analyses of phase difference within each arm will be carried out multiple comparison adjustment. Model diagnostics will be carried out to confirm the distributional assumptions and appropriate corrective actions (e.g. transformation) will be performed as needed.

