Two types of fatigue-related measures will be collected from the Actiwatch-S. The first is a daytime activity count per minute, which is calculated by dividing the total daily activity counts by the total daytime minutes. For each phase as defined above, we shall use the corresponding 21-day (or 28-day) average as appropriate. The second type of measure is obtained from the four self-reported readings of the VAS-F. The daily averages are obtained from the non-missing entries each day, and are then combined to provide the phase average the same way as the daytime activity count. The analytical framework is identical to that for BFI, albeit with the changed outcome.

A secondary analysis with BFI will also be carried out which investigates the difference in proportion of severely fatigued subjects (BFI ≥ 6) across the three study arms. The analytical framework will be that of a mixed-effects logistic regression model with severe BFI (yes/no) being the dichotomous outcome. Apart from group, phase, and group*phase interaction as primary covariates, the model will also be adjusted for baseline status of severity. Remaining covariates in the model are identical to those in the continuous BFI model. The clustering effect due to subject will be accounted for using a generalized estimating equations approach.

In order to assess the extent of association between the improvement in FACT-B and improvement in fatigue measure (specific aim #1 letter D), we shall create the change-scores (week 6 – baseline, week 10 – baseline) for FACT-B (both total and component scores), and BFI. Then we shall fit a linear mixed model similar to that for the original BFI analysis, with BFI change-score as outcome, and the FACT-B change-score as a time-varying covariate. There will not be any phase or week variable in the model. We shall restrict this analysis to the SA and RA arms only so that the group variable will consist of two levels. A group*FACT-B interaction in the model will investigate any differential association across the arms between the change-scores. The additional covariates and clustering adjustment would be similar to the BFI analysis.

Secondary Aims:

1. Assessing difference across study arms with respect to sleep parameters

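### The daytime activity outcome is defined with a whole-day numerator over a daytime-only denominator, so night movement enters a score labelled daytime

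*Protocol article*

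**What the plan says.** The aims list, as item B of the primary aim, "objective daytime physical activity on a wrist worn accelerometer using average activity counts/minute". The statistics section describes the same outcome in two ways. When it introduces the three fatigue outcomes it speaks of "a measure of average daily physical activity and a self-reported fatigue score, both based on Actiwatch-S data". When it turns to the Actiwatch measures it writes "The first is a daytime activity count per minute" and says this is "calculated by dividing the total daily activity counts by the total daytime minutes". These values are averaged over 21 or 28 days to give the phase score, which is then analysed in the same framework as the BFI.

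On wear, the section on the objective measure states: "Participants are instructed to wear the Actiwatch-S at all times". The heading of that section reads "Actiwatch-S is used to collect daytime and nighttime physical activity and symptoms", so night counts are recorded by the same device. On removal it says: "If the Actiwatch-S is removed, removal and replacement times are recorded in a daily log book". The software's output consists of "standard parameters of sleep/wake and activity cycles for each day of recording, which are checked by our study staff using the log books".

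**The concern.** A rate per minute needs its counts and its minutes to come from the same period. Here the counts are described as daily and the minutes as daytime. Because the watch also records at night, the stated formula adds movement during sleep to the numerator without adding the matching minutes to the denominator. No sentence in the article limits the counts to daytime.

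This matters more here than in a trial without a sleep hypothesis. The trial expects relaxation acupressure to improve sleep, so night movement may differ by arm, and part of a sleep effect could then appear in the activity outcome. Of the three fatigue outcomes in the statistics section, activity is the only one that is not self-reported. The article also concedes that women cannot be blinded between acupressure and standard of care, which adds to the value of a clean device-based measure.

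**Working it through.** The article gives no mean, standard deviation or effect size for activity counts, so there is no figure to reproduce. The size is illustrated with assumed inputs.

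**Formula.** Let M be daytime minutes, D the true daytime rate and c the night rate, in counts/min. The literal score is [D·M + c·(1440 − M)] / M. The intended score is D.

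**Step 1: inflation of the level.** Assume M = 960, D = 200 and a 480-minute night. The score is 200 + c·480/960 = 200 + c/2.
- c = 10: 205, or +2.5%
- c = 20: 210, or +5.0%
- c = 30: 215, or +7.5%

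As a second set of assumptions, let the night rate be a fraction f of the daytime rate. The ratio of literal to intended score is then 1 + f·(1440 − M)/M.
- M = 1020, f = 0.02: 1 + 0.02 × 420/1020 = 1.008
- M = 900, f = 0.10: 1 + 0.10 × 540/900 = 1.060

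Over these ranges the inflation runs from 0.8% to 6.0%.

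**Step 2: shift when night movement falls in one arm, daytime activity unchanged.** With the inputs of step 1 and a 20% fall in c:
- c from 10 to 8: 204/205, or −0.5%
- c from 20 to 16: 208/210, or −1.0%
- c from 30 to 24: 212/215, or −1.4%

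If night movement instead halves, the shift runs from −1.0% (M = 1020, f from 0.05 to 0.025) to −2.8% (M = 900, f from 0.10 to 0.05: 1.03/1.06).

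**Step 3: opposing effect of longer sleep.** Suppose daytime minutes follow the wake interval and sleep lengthens by 30 minutes, giving 930 wake and 510 night minutes.
- Longer sleep alone, c = 20: 200 + 20 × 510/930 = 210.97 against 210, or +0.5%
- Longer sleep with c reduced to 16: 200 + 16 × 510/930 = 208.77 against 210, or −0.6%

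The two parts of a sleep improvement pull the score in opposite directions. The sign of the net shift depends on their relative size, which the documents do not give.

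**The case against.** The strongest reply is that daily is loose wording for daytime. The sentence that holds the formula calls the result a daytime count, the aims do the same, and the statistics section elsewhere calls the same outcome daily, so the two words may be interchangeable to the authors. That reading is plausible, but it is not secure. The formula uses both words for the two halves of one ratio, and nothing restricts the counts. Two programmers could follow it in good faith and obtain different values.

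It can also be said that an inflation common to all arms largely cancels in a randomised comparison adjusted for baseline. That stands. Only a difference between arms in night movement or sleep length would bias the contrast. The shift shown for a 20% fall in night movement is about 1%, rests on assumed rates, and has no standard deviation in the article to be judged against.

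A reader might go further in two ways, and the documents support neither:
- **That off-wrist minutes stay in the denominator, so non-wear counts as inactivity.** This would be inferred only from the word total. The article logs removal times and has staff check the software's parameters against the log books. Detailed wear-time rules are what an article commonly leaves to the full protocol or analysis plan. If such minutes were kept, 60 of them in a 960-minute day would lower the score by 60/960 = 6.3%, but no sentence says that they are.
- **That the score does not measure daytime activity at all.** On the assumed rates, daytime counts make up 93% (200/215) to 98% (200/205) of the numerator. It is a daytime rate with some night movement mixed in.

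**Conclusion.** The point holds for the mismatch between numerator and denominator. Followed as written, the formula does not give the quantity it names. Under assumed rates the inflation is a few percent, 0.8% to 7.5% across both sets of assumptions. A difference between arms in night movement would shift the score by roughly 1%, or up to 2.8% if night movement halves. The net direction under a sleep improvement is uncertain. All of these figures depend on assumed day lengths and count rates.

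The consequences are limited. The BFI remains the primary outcome and the basis of the main power calculation, so neither the sample size nor the stated power changes. The correction is still worth making, because it removes an avoidable route by which a sleep effect could enter the device-based activity outcome.

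**What to change.** Define the outcome as activity counts recorded during the daytime (wake) interval, divided by the minutes of that same interval. Take the interval from the Actiware sleep/wake scoring and the diary or log-book entries. Use this one definition in the aims and in both places in the statistics section where the outcome is named, replacing the description as average daily activity.

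A sensible companion detail is to use the logged removal times to limit both counts and minutes to worn time. It can sit in the analysis plan if it is not already there.

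The cost is one sentence, aligned wording in three places and minor programming. No new data are needed, since continuous actigraphy, sleep/wake scoring and removal times are already collected.

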#### Pre-baseline

The PI reviews the documents and confirms the eligibility for the study candidate. An Actiwatch-Score (hereafter referred to as Actiwatch-S; Phillips Respironics, Bend OR), a wrist-worn accelerometer, and a study log book along with instructions are mailed to them. An Actiwatch-S is a wristwatch-like device that continuously measures activity levels and also allows for input of fatigue severity scores. The device is worn by the participant throughout the study period. The study log book accompanies the Actiwatch-S and has additional questions about activity and sleep quality to be completed within and across days in the study. The participants enter their fatigue scores in the log book as they do in the Actiwatch-S, which provides a cross-validation of the time-stamped fatigue entries. The participants are instructed to wear the Actiwatch-S for one week prior to the Baseline Visit and to record their fatigue three times a day at pre-scheduled times after hearing an audible alarm. Prior to the Baseline appointment, the participant is randomized into one of the three arms.

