#### Visit 2- baseline visit (week 0)

At the visit participants fill out questionnaires as indicated in Table
2. If the participants are randomized into one of the acupressure treatment arms, they are given acupressure instructions by the study nurse. A DVD, a handout describing acupressure, and illustrations of the proposed acupressure points are also given to the participants. On this visit the participant returns the Actiwatch-S and the study logbook. The data from the Actiwatch-S are downloaded and the watch is reinitialized and given to the participant along with a new log book.

**Table 2 T2:** Study Visits

	**Visit 1**	**Daily**	**Visit 2**	**Visit 3**	**Visit 4**	**Weekly Phone Calls**	**Visit 5**
	**Screening (within 60 days of baseline)**	**Days (−7 to 70)**	**Baseline Week 0**	**Week 3**	**Week 6**	**Week (−1, 1–2, 4–5 & 7–9)**	**Week 10**
Laboratory Values ^1^	X						
Medical Exam/History/Socio-demographics	X						
Urine Pregnancy Test ^1^	X						
PRIME-MD^2^	X						
HADS ^2^	X				X		X
BFI ^2^	X		X	X	X	X	X
Concomitant Medication & Supplements	X						
Sleep Diary	X				X		
Group Randomization ^3^			X				
Actiwatch Data Collected		X	X^4^	X^4^	X^4^		X^4^
LTQL			X		X		X
BSAPQ ^2^	X		X		X		X
GSE ^2^			X		X		X
BPI^2^	X		X		X		X
Study Logbook		X	X	X	X		X
PSQI ^2^	X				X		X
VAS for Pain ^2^	X						
Berlin Questionnaire	X						
Therapy Evaluation Questionnaire			X		X		
Perform Acupressure ^5^			X	X	X		
Assess Treatment Fidelity – Self efficacy Measure				X	X		
Adverse Events				X	X	X	X
Assessment of Blinding					X		

^1^ Complete Blood Count; blood for correlative tests, blood for future DNA analysis, Urine pregnancy test as appropriate.

^2^ HADS = Hospital Anxiety Depression Scale; BFI = Brief Fatigue Inventory; and PSQI = Pittsburgh Sleep Quality Index; LTQL = Long Term Quality of Life Instrument; BSAPQ = Breast and Surrounding Areas Pain Questionnaire; GSE = General Self Efficacy Scale; BPI = Brief Pain Inventory; VAS for Pain = Visual Analog; PRIME-MD = *Primary Care Evaluation of Mental Disorders.*

^3^ Participants are randomized to one of three treatments: Standard of Care; Relaxation Acupressure; or Stimulating Acupressure.

^4^ Data file downloaded at these visits.

^5^ Does not apply to standard of care arm.

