#### Visit 4 (week 6)

Marks the end of doing acupressure and the beginning of the follow-up phase: Participants complete a battery of questionnaires, are asked about any adverse events, assessed for blinding, and tested for acupressure fidelity (see Table
2). Data from the Actiwatch-S are downloaded and the reinitialized and a14-day sleep diary is given to them. If the participant belongs to the acupressure treatment arm of the study they are asked to stop acupressure treatment for the next 4 weeks.

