### Study measures

#### Subjective study measures

Below is a list of self-report measures that participants complete per the schedule in Table
2.

*Hospital Anxiety Depression Scale):* this 15-item questionnaire is a widely used instrument to measure depression and anxiety
[15].

*Primary Care Evaluation of Mental Disorders (PRIME-MD):* It is a 26-item self-administered questionnaire that screens for five of the most common groups of psychiatric disorders in primary care: depression, anxiety, alcohol, somatoform and eating disorders
[16].

*Brief Fatigue Inventory:* The BFI assesses the severity of fatigue and the impact of fatigue on daily functioning in patients with fatigue due to cancer and cancer treatment
[17].

*Actiwatch-S to collect fatigue severity:* Four times daily participants indicate on a scale from 0 = “No Fatigue” to 10 = “Extremely Fatigued,” their fatigue severity at that moment. These scores are entered into the Actiwatch-S upon completion of their acupressure treatment and at three pre-scheduled times, once in the morning (9:00 AM), once in the afternoon (3:00 PM) and once in the evening (9:00 PM).

*Long Term Quality of Life Instrument:* The LTQL is a 34 items questionnaire that is self-administered for evaluating functional impairment and the perceived effect of that impairment on quality of life in breast cancer survivors
[18].

*Breast and Surrounding Area Pain Questionnaire:* The BSAPQ is used for measuring pain in the area of the breast (defined as the breast, armpit, side of the body, or arm on the operated side) on either the operated breast or the area from which the breast was removed
[19].

*Brief Pain Inventory:* The BPI is used to assess average clinical pain
[20].

*General Self-Efficacy Scale:* The construct of Perceived Self-Efficacy reflects an optimistic self-belief that one can perform a novel or difficult task, or cope with adversity in various domains of human functioning
[21].

*Pittsburgh Sleep Quality Index:* The PSQI evaluates sleep disturbance over the past month.
[22]. *Sleep Diary:* Sleep diaries are simple, non-invasive, self-report measures that provide night-to-night information on sleep pattern, quality, and relevant daytime behavior.

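### The daily VAS-F average includes a post-acupressure reading with no defined counterpart in standard of care, the baseline week or washout, so it is not like-for-like

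*Protocol article*

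**What the plan says.** Under Subjective study measures, participants rate momentary fatigue from 0 to 10 four times a day. The article then says when: "These scores are entered into the Actiwatch-S upon completion of their acupressure treatment and at three pre-scheduled times", the scheduled times being 9 AM, 3 PM and 9 PM. In the week before the baseline visit the instruction is different: women "record their fatigue three times a day at pre-scheduled times after hearing an audible alarm".

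The row for performing acupressure in Table 2 carries footnote 5: "Does not apply to standard of care arm". At week 6 the women in the acupressure arms finish treatment, and "they are asked to stop acupressure treatment for the next 4 weeks".

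The analysis rule is in Statistics and power analysis: "The second type of measure is obtained from the four self-reported readings of the VAS-F", and "The daily averages are obtained from the non-missing entries each day". The daily means are then averaged within phase (weeks 1-3, 4-6 and 7-10). For the model: "The analytical framework is identical to that for BFI, albeit with the changed outcome". In the BFI framework, "Of primary interest is the group*phase interaction", with the baseline value as a covariate.

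The daily average VAS-F is also the fatigue measure for time to onset (first fall of 3 points from baseline) and time to relapse (first rise of 3 points from the six-week value). Both are analysed in the acupressure arms.

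**The concern.** Three of the four readings are tied to the clock and can be taken by every woman on every day. The fourth is tied to finishing a session. As written, it arises only in the relaxation (RA) and stimulating (SA) arms, only in weeks 1-6, and only on days when a session is done. Averaging whatever is present therefore sets a mean that includes an immediate post-session rating against a mean that does not. The difference in make-up follows arm and phase, the two factors the model tests.

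The article itself gives reasons to expect the post-session rating to differ from the scheduled ones. The Discussion stresses that fatigue varies a good deal within a day, and the instructions set no clock time for the session. The Discussion also concedes that women know whether they were assigned acupressure or standard of care, so a rating given straight after a session is open to expectation. At stake is whether a VAS-F difference means less fatigue through the day or an acute response captured in one arm-specific reading.

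**Working it through.** **Inputs.** The article states no power, variance or expected effect for VAS-F, so there is no figure to reproduce. The reading schedule and averaging rule are as set out above. Let d be the post-session reading minus the mean of the scheduled readings. The article does not give d; I assume -0.5 to -3.

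**Step 1: readings defined per day.**

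| | Baseline week | Weeks 1-6 | Weeks 7-10 |
|---|---|---|---|
| RA, SA | 3 | 4 on session days, otherwise 3 | 3 |
| Standard of care | 3 | 3 | 3 |

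No text excludes the post-session reading from the mean or defines a substitute for it elsewhere.

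**Step 2: shift in one day's mean.** With scheduled mean m and all entries present, (3m + (m + d))/4 - m = d/4. With only k scheduled entries present it is d/(k + 1): d/3 if one is missed, d/2 if two are, and d if all three are. If a fraction a of days has a session, the phase mean with complete entries shifts by a·d/4.

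**Step 3: where the shift goes.** Relative to standard of care, RA and SA shift by 0 at baseline, a1·d/4 at mid-treatment, a2·d/4 at end-treatment and 0 in washout.

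- Acupressure versus standard of care on treatment: the full shift. Adjusting for a three-reading baseline does not remove it.
- Mid- to end-treatment: (a2 - a1)·d/4, which is zero if adherence is stable.
- End-treatment to washout: a change of -a2·d/4 in RA and SA only, which is a group*phase pattern.
- RA versus SA: zero if d, timing and adherence are the same in both arms.

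**Step 4: illustrative effect on the tests.** Assume no difference in the scheduled readings, full adherence, 100 women per arm, and the BFI variance components from the Power analysis section (4 and 4) borrowed for VAS-F. These inputs are rough even for BFI: with residual variance 4, a noncentral F gives a BFI interaction power of 0.73 against the stated 0.82, which rests on 100 simulations. With s = |d|/4, the three-arm, three-phase interaction has noncentrality 100 × (4/9) × s²/4 on 4 and 594 degrees of freedom. The on-treatment contrast of pooled acupressure against standard of care has standard error √[(4 + 4/2)(1/100 + 1/200)] = 0.30.

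| d | Shift | Group*phase rejection (nominal 5%) | Acupressure vs standard of care rejection (nominal 5%) |
|---|---|---|---|
| -0.5 | -0.125 | 5.9% | 7.0% |
| -1 | -0.25 | 8.7% | 13.3% |
| -2 | -0.50 | 22.6% | 38.5% |
| -3 | -0.75 | 48.4% | 70.5% |

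With variances of 2 and 2 the group*phase column becomes 6.8%, 12.9%, 43.4% and 81.7%. With 80% adherence and d = -2 (variances 4 and 4), the shift is -0.40 and the group*phase figure 15.5%.

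**Step 5: onset and relapse.** Baseline has three readings and session days have four, so an observed 3-point fall needs a fall of only 3 - |d|/4 in the scheduled readings. For d of -1, -2 and -3 that is 2.75, 2.50 and 2.25. If the six-week value is an on-treatment mean, losing the fourth reading adds |d|/4 to the later rise, so the relapse threshold drops to the same values.

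**The case against.** The strongest reply is that little of the trial's main inference is touched. A reader might infer that the primary result is compromised. It is not: BFI is the stated primary outcome, comes from separate questionnaires and calls, and is the basis for power. The interaction powered at 0.82 compares mid- with end-treatment BFI; even in VAS-F, that part of the interaction is free of the shift under stable adherence.

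A reader might also infer that stopping acupressure creates spurious relapses. With complete entries it cannot do so alone: even d = -3 adds 0.75 to a criterion of 3. Nor does the article support a general claim that RA versus SA is biased. Both arms gain the extra reading and both lose it, so a common d cancels to first order, in the phase model as in onset and relapse. Bias there needs a difference in acute response, timing or adherence. That is plausible, since the Background cites greater sleepiness after RA than SA, but it is not established.

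The article also speaks of four daily ratings without separating the arms, and footnote 5 concerns performing acupressure, not entering a score. A fuller protocol could specify a fourth reading for standard of care or washout. The supportable statement is therefore that no matching reading is defined, not that these women never give one.

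Finally, d is assumed. At d = 0 there is no bias, at d above zero it reverses, and at d = -0.5 the interaction test stays close to nominal.

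All of this stands and limits the point. It does not remove it: the averaging rule is stated, the three-reading baseline week is explicit, and nothing in the article makes the means comparable.

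**Conclusion.** The point holds in limited form and should be fixed. As written, daily VAS-F is not the same quantity in acupressure and standard of care, or in baseline, treatment and washout. The structural shift is d/4 per session day with complete entries and larger when scheduled entries are missed: -0.125 to -0.75 points for an assumed d of -0.5 to -3. It affects acupressure versus standard of care on treatment and the treatment-versus-washout part of group*phase. For negative d it also distorts absolute onset and relapse times in both acupressure arms, and the article wants those times to guide clinical implementation. RA versus SA is affected only under the added conditions above.

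The existence of the mismatch rests on the text. Its size and direction rest on d, and the rejection rates also rest on borrowed BFI variances, so they are illustrations and not forecasts.

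**What to change.** Define daily VAS-F as the mean of the 9 AM, 3 PM and 9 PM readings, in all arms and all periods including the baseline week. Use that one definition for the phase averages, the baseline covariate, onset and relapse. Report the post-acupressure reading separately, within RA and SA, as an acute response.

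This sets the structural shift to zero whatever d is. It needs no new data: Actiwatch-S entries are time-stamped and the logbook records when acupressure was done, so the post-session entry can be identified. The cost is a short change to the endpoint definition and one fewer reading per treatment day in the acupressure arms.
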